### Secondary outcomes

Our secondary outcome is treatment adherence for depression care. This will be determined based on the number of participants who initiate treatment one-month post-intervention and continue to engage in care during the three-month follow-up period. General linear regression models will be used to test the secondary outcomes as well.

### Mediators

Previous studies have demonstrated a positive correlation between mental health literacy, attitudes, stigma, and symptom severity in relation to help-seeking behaviour [10, 11, 29, 69]. Our formative study also indicated that individuals who were familiar with depression symptoms and aware of mental health service providers and locations were more inclined to seek help from health care providers. Therefore, we aim to investigate whether participants’ knowledge, attitudes, and stigma can act as mediators in influencing help-seeking behaviour. Furthermore, we will also assess the symptom severity of depression, as measured by the PHQ-9 at a three-month follow-up, to determine if it plays a mediating role in help-seeking behaviour. We will use the Baron and Kenny method along with a path analysis to examine the mediation effects. For the Baron and Kenny method, a series of general linear regression models will be tested to assess mediation [49]. Mplus will be used to conduct a path analysis looking at the direct and indirect effects to determine if the hypothesized mediator is in fact a mediator in the relationship between the predictor variable and outcome of interest [19].

### Moderators

We will assess how socio-demographic factors such as caste/ethnicity, age, gender, education level, occupation, and religion moderate the intervention’s impact through general linear regression models and interaction variables. Previous studies in Nepal have shown that gender, caste/ethnicity, and occupation can affect rates of depression and anxiety [39, 48]. These analyses are crucial for promoting equitable access to mental health care in Nepal.

### Qualitative data analysis

Each interview or focus group discussion will be recorded and transcribed in Nepali immediately after the fieldwork. The transcripts will then be translated into English for analysis by a skilled translator. Two members of the research team will independently code 10% of the interviews or focus group discussions following the CFIR guidelines. A review of all the codes for each interview will be carried out until the research team members reach a consensus on the codes to be applied to specific text segments. Once consensus is reached, interview transcripts will be entered, coded, and analyzed in NVIVO.

### Dissemination

We will share the results with key stakeholders in Kanepokhari Rural Municipality and Patharisanischare Municipality. Additionally, we will organize a dissemination programme in Kathmandu for stakeholders involved in mental health, including senior officers from the Ministry of Health and Population, representatives from non-governmental organizations, international non-governmental organizations, and other civil society organizations. The study findings will also be published in academic journals.

### Timeline

The training of FCHVs on CIDT and on Gain Life intervention began in May. They began implementing CIDT and the intervention in June. Data collection for the baseline survey commenced in July 2024. The enrollment and assessment schedule, following the SPIRIT guidelines, is outlined in Fig. 2 below. The protocol was developed in strict adherence to the Standard Protocol Items: Recommendations for Intervention Trials 2013 (SPIRIT) guidelines [6].

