### Recruitment

Participants will be purposefully recruited through a systematic process. Trained FCHVs will identify potential participants who meet the CIDT criteria, such as individuals whose personal experiences align significantly with the CIDT story, exhibit impaired daily functioning, and express a need for support. Once identified, FCHVs will provide the details (age, gender, location) of individuals who meet CIDT criteria to their supervisor via a phone call. The supervisors will assess the eligibility criteria (i.e. 18 years or older, ability to speak, and CIDT threshold) and send the case details to the first author ([name]) for randomization.

Bi-monthly group meetings will be held for FCHVs to share their progress, discuss challenges encountered during the implementation of the CIDT, and provide motivation. Supervisors will also conduct field visits to offer immediate feedback and enhance FCHVs’ skills in utilizing the CIDT to ensure an effective recruitment strategy.

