### Randomization

Participants will be randomly assigned to one of eight treatment conditions based on four factors: (i) information on depression, (ii) available treatments, (iii) stigma reduction through myths and facts, and (iv) life transformation experiences. Using Microsoft® Excel (Version 16.86), a list of random numbers between one and eight with no duplicates was generated for each FCHV. As the FCHVs enrol participants, the first author assigns the next random number on their list to each participant, indicating the allocated treatment condition. Because each FCHV will recruit between 8 and 10 participants and there are only 8 treatment conditions, some FCHVs ended up delivering each condition at least once, and some conditions will be delivered twice. The table below summarizes the allocation of participants into different intervention components.

The first author will randomize each case using a computer-generated random table and assign them to one of the eight factors presented in Table 1 below. The randomization will be conducted separately for each FCHV to ensure cases are allocated to all 8 factors. The first author will inform the supervisors of the randomization results within 24 h. The supervisors will then inform FCHV which intervention or combination of interventions should be delivered to each case via a phone call.

**Table 1 Tab1:** Random allocation of participants into different intervention components

Experimental condition/factors	Information about depression	Information about available services	Stigma reduction	Recovery story (video)	Sample size
1	**✓**	**✓**	**✓**	**✓**	36
2	**✓**	**✓**	**✓**		36
3	**✓**	**✓**		**✓**	36
4	**✓**	**✓**			36
5	**✓**		**✓**	**✓**	36
6	**✓**		**✓**		36
7	**✓**			**✓**	36
8	**✓**				36

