## Outcome measures

### Primary outcome

#### Help-seeking behaviour

Changes in help-seeking behaviour will be assessed by determining if participants sought mental health treatment within one month after attending the FCHVs intervention. Mental health treatment is defined as treatment provided by health care providers including trained primary health care workers, doctors, and mental health specialists. This does not include treatment provided by traditional healers and religious leaders. Research assistants, who are unaware of the participants’ assignment to the intervention, will visit their homes one month post-intervention. They will inquire about the participants’ interactions with FCHVs, the places/providers they visited for seeking care, and the reasons for choosing a specific provider using a semi-structured questionnaire. We will not verify the accuracy of the treatment they received. Participants who did not seek treatment will also be asked about the reasons for not seeking care and their plans to seek treatment soon. Participants will be asked a “yes” or “no” question: “Did you seek help for your health issue after attending the FCHV session?” with a yes or no response. We will report the percentage of participants who respond “yes” to this question as an indicator of seeking treatment.

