### Secondary outcome

#### Treatment adherence

Treatment adherence will be monitored by following up with participants for three months after they start treatment. The three-month follow-up period was chosen based on feasibility and previous studies [17, 33]. Participants who begin treatment one month after the FCHVs intervention will be followed up after three months to evaluate their ongoing care. During the follow-up, participants will be asked if they are still receiving care from the same providers, if they have switched providers, or if they have stopped treatment. Participants who switched providers will be asked about the reasons for the change, while those who discontinued treatment will be asked about the reasons for their decision to stop receiving services. Participants will be asked “yes” or “no” questions: “Have you been receiving treatment for your health issues since we last met three months ago?” We will report the percentage of participants who respond “yes” to this question as an indicator of treatment adherence.

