### Quantitative data analysis

Quantitative data analysis will be conducted using StataIC 15.1 and MPlus (v8) [60]. Baseline characteristics of the participants (such as age, sex, caste/ethnicity, education) will be compared to assess balanced randomization. An intent-to-treat model will be used. Participants who do not receive all allocated intervention components for various reasons will be included in the intent-to-treat analysis. Despite the short three-month interval between the baseline and follow-up interviews, there is a risk of participant dropout during the follow-up period, possibly due to work-related mobility. To address this issue, we also plan to conduct the follow-up interviews via phone to minimize the risk of dropout. Any missing data or loss to follow-up will be carefully examined, and if necessary, we will utilize multiple imputation techniques to handle missing data effectively.

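### Intervention delivery began in June but the baseline survey only in July 2024, so participants treated before the survey opened have baseline data from after randomisation and treatment

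*Protocol article*

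**What the plan says.** The Timeline section dates the two starts in consecutive sentences: "They began implementing CIDT and the intervention in June. Data collection for the baseline survey commenced in July 2024".

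The path to treatment is set out under Recruitment and Randomization. After the FCHV phones in age, gender and location, "The supervisors will assess the eligibility criteria (i.e. 18 years or older, ability to speak, and CIDT threshold) and send the case details" for randomisation. The result goes back to the supervisors within 24 hours, and "The supervisors will then inform FCHV which intervention or combination of interventions should be delivered to each case via a phone call". No research interview is named along this path. The section on the implementation process also goes straight from the FCHV's consultation and the person's agreement to scheduling the session.

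Under Blinding, baseline interviews are the job of blinded data collectors, not FCHVs. The first research-assistant contact that the text describes is the primary-outcome assessment, for which they "will visit their homes one month post-intervention".

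Three other statements bear on timing:
- Quantitative data analysis: "Despite the short three-month interval between the baseline and follow-up interviews".
- Treatment adherence, follow-up item: "Have you been receiving treatment for your health issues since we last met three months ago".
- Feasibility, acceptability and appropriateness: continued care is dated at three months after taking part in the intervention.

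The baseline data have a stated use. Under Quantitative data analysis, characteristics such as age, sex, caste/ethnicity and education are compared to judge whether randomisation was balanced. Moderators adds occupation and religion, among others, as effect modifiers.

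**The concern.** A baseline is useful because the allocation cannot have influenced it, neither the values recorded nor who is there to be recorded. Data collected after allocation and treatment lose that protection in two ways.

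First, the table covers only people reached for the interview. If loss between allocation and interview differs by condition, the table mixes chance imbalance with differential loss and cannot show whether randomisation worked. The article itself expects dropout from work-related mobility.

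Second, anything that can change after a session or after seeking care may already reflect the intervention. Among the listed moderators, occupation is the clearest case. An interaction with a post-treatment occupation is not an interaction with a pre-randomisation characteristic.

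**Working it through.** The question is one of order, so the check sets dates and intervals side by side.

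**Step 1: order of the two starts.** Intervention: "They began implementing CIDT and the intervention in June" (year taken as 2024). Survey: "Data collection for the baseline survey commenced in July 2024". The day of the month is not given.
- Shortest gap: 30 June to 1 July = 1 day.
- Longest gap: 1 June to 31 July = 60 days.

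The gap is positive on every reading. Because the allocation is relayed to the FCHV before delivery, whoever was treated before the survey opened was also randomised before it.

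**Step 2: how many.** The article gives no enrolment by month, so the count cannot be derived. Purely as an illustration, assume even enrolment over 4 to 8 months and delivery throughout June: 288/8 = 36 and 288/4 = 72, or 12.5% to 25%. Both assumptions are outside the document. If the first sessions fell in late June, the number could be very small.

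**Step 3: where the baseline interview sits for everyone else.** Put the intervention at month 0 and the one-month visit at month 1. The three-month interval under Quantitative data analysis then places baseline at follow-up minus 3.

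| How the follow-up is dated | Follow-up | Implied baseline |
|---|---|---|
| Three months after the one-month visit (reading of the adherence item) | 1 + 3 = 4 | 4 − 3 = 1, the one-month visit |
| Three months after treatment starts, with the start between months 0 and 1 (Treatment adherence; Symptom severity) | 3 to 4 | 0 to 1 |
| Three months after the intervention (Feasibility section) | 0 + 3 = 3 | 3 − 3 = 0, around delivery |

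In the first row a pre-allocation baseline would lie at least 4 months before follow-up, against the stated three. In the third row the one-month visit would be 3 − 1 = 2 months before follow-up, which does not match the three months in the adherence item. The stated intervals therefore do not fit one schedule, and they do not settle where baseline falls.

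**Step 4: what the late timing touches.**
- Age, sex, caste/ethnicity and education, the named balance variables, are essentially fixed over this span. Their values are sound; the weakness is in who appears in the table.
- The knowledge and stigma scales are stated not to be asked at baseline, and the PHQ-9 is described only at three months after treatment initiation. Neither is affected.
- Occupation can change, so it is exposed.
- The primary outcome is one post-intervention yes/no item compared by randomised component, and no baseline covariate is named for it. It is little affected.

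**The case against.** The strongest reply is that the schedule is in Fig. 2, with the recruitment map in Fig. 1, and neither is shown. A condensed article also need not list every step: the recruitment path omits the written-consent step too, although eligibility requires consent. Silence about a pre-allocation interview does not show that there was none. This stands for participants enrolled once the survey was running. It does not help those treated earlier, because no schedule can give them a pre-treatment interview in a survey that had not opened. The pilot does not explain the June start either: it took place in a different district, and the Timeline describes this study.

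A reader might go further and infer that baseline simply is the one-month visit, so that all 288 participants lack a pre-intervention assessment. The documents do not support this. The primary-outcome section never calls that visit baseline. The adherence item refers only to the most recent meeting, which would be the one-month visit whether or not an earlier interview took place. The Feasibility section dates its three-month point from the intervention, which would put baseline near delivery. The related worry, that multiple imputation would have almost nothing to draw on for people lost before the visit, depends on the same inference. It also overlooks the allocation, the FCHV and the planned telephone follow-up.

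It is also fair to say that the harm is limited. The balance variables are nearly fixed, and a material change of occupation within about a month is possible rather than demonstrated. Delivery is already under way, so part of the remedy comes too late for those already treated.

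**Conclusion.** The concern holds in a limited form. On the article's own dates, participants treated before the survey opened can have only post-randomisation, post-intervention baseline data. Their number is not given, and the 36 to 72 above is an illustration rather than an estimate. For later participants the timing is undetermined: the text never places the interview before allocation, and its stated intervals conflict.

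Two uses are weakened: the check that randomisation was balanced, and moderator analyses on changeable items such as occupation. The primary comparison by component is little affected. The conclusion assumes that June means June 2024 and that the June deliveries were to trial participants, as the Timeline implies. It is worth correcting because the correction is specific and nearly free.

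**What to change.** 1. For participants still to be enrolled, collect the baseline items after consent and before the allocation is released. The supervisor's eligibility step and the 24-hour allocation window already provide the slot.
2. For those treated before being interviewed, treat as baseline only the recruitment-call data (age, gender, location) and fixed attributes such as sex and caste/ethnicity. Label changeable items such as occupation as post-intervention, and keep them out of balance checks and confirmatory moderator claims.
3. Assess balance, and report attrition by condition, from the full list of randomised participants rather than from those interviewed. State how many were interviewed only after their first session.
4. Reconcile the timing in Help-seeking behaviour, Treatment adherence, Feasibility, Quantitative data analysis and Timeline. Say when the baseline interview occurs relative to allocation and the first session, and from which event the three months are counted.

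This needs changes of wording and a short question set moved earlier, with no extra participants. The downside is less baseline information for those already enrolled and a slightly longer recruitment contact.

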**Fig. 2 Fig2:**
[figure not shown]
Schedule of enrolment, interventions, and assessments

## Discussion

In this study, we utilized the MOST framework to optimize a community-based intervention aimed at increasing help-seeking for depression care. Through a factorial design, our goal is to develop an effective intervention that raises awareness about depression, available services, and reduces stigma. The study will examine the impact and interaction of intervention components such as depression information, treatment awareness, dispelling myths, and life transformation experiences. The primary outcome will be changes in help-seeking behaviour, with treatment adherence as a secondary outcome.

The strengths of our study include the following: (i) the use of multiple methods and stakeholders in the development of the intervention, such as a systematic review, formative study, consultative workshops with various stakeholders, and pilot testing with a group of 10 FCHVs in another district; (ii) while most global mental health research focuses on developing and evaluating interventions to address supply-side barriers, this study targets demand-side barriers by using the innovative study design MOST, enabling us to evaluate the effectiveness of intervention components through an iterative optimization process; and (iii) the implementation of the intervention and study in multicultural, multilingual, and multi-ethnic communities in eastern Nepal, allowing for generalization of results throughout Nepal.

We anticipate challenges in maintaining intervention fidelity, as participants may seek additional information from FCHVs beyond what is included in the intervention packages or in a particular component. Additionally, ensuring fidelity in delivering the core components and the combination of intervention packages by the same FCHVs may be challenging. To address this, fidelity checklists will be used to guide delivery, and regular supervision sessions will be conducted to support FCHVs in maintaining fidelity.

The study has some limitations, including being single-blinded, with only RAs and the statistician blinded to the study allocation. We have included four intervention components, including information about depression as the core component and three candidate components, due to resource constraints. There may be other factors influencing help-seeking for depression that were not included in this study. The results will guide decisions on progressing to a fully powered randomized controlled trial and further optimization with new intervention components.

## Data Availability

Data sharing is not applicable to this article as no datasets were generated or analyzed in the current study.
